#### Saliva collection

Participants will be provided with a package containing written instructions for saliva collection and Salivette collection devices (Sarstedt, Nümbrecht, Germany). Three saliva samples will be collected on one morning: one immediately upon awakening without rinsing the mouth with water, one 15 min and one 30 min after. To avoid contamination of saliva, participants will be asked not to brush their teeth, drink or eat at least 60 min before sampling.

Saliva samples will be centrifuged at 4 °C (1,000 rpm, 2 min; Hettich MR22) and stored at − 80 °C until assayed. The samples will be assayed for salivary-free cortisol as a duplicate in a single assay batch per participant via commercially available enzyme immunoassay (IBL International GmbH).

#### Measurements at birth

Within two hours after delivery, midwives will measure birth weight to the nearest 10 g using an electronic scale and measure recumbent crown-heel length to the nearest 0.5 cm. Additionally, head circumference, Apgar scores at 1, 5, and 10 min, as well as umbilical blood pH will be obtained from the hospital delivery logs, clinical examination, and medical records. To assess neonatal leanness, the neonatal Ponderal index will be calculated as PI = 100x(kg/m^3^). Gestational age at birth will be calculated from the last menstrual period and verified by first-trimester ultrasound measurements. Small (SGA) and large for gestational age (LGA) neonates will be defined as live-born infants below the 10th or above the 90th percentile of birthweight for gestational age, respectively, according to German reference curves [48].

#### Physical activity assessment

The Actigraph wGT3X-BT (Actigraph, Florida, US) will be used to determine physical activity levels based on total physical activity and step counts at three points in time over 3 days (weeks 12, 20, and 28 of gestation) from all participants (intervention and control group). Activity counts, recorded every minute, will be added up to provide total counts per day and converted to metabolic equivalent of tasks (METs) in specific intensity levels [49]. Furthermore, we will use the Pregnancy Physical Activity Questionnaire (PPAQ) as described by Chasan-Taber et al. [50] for all participants to detect physical activity at the beginning of pregnancy (week 8 of gestation), during pregnancy (week 14, 24 of gestation) and at the end of pregnancy (week 36 of gestation). Self-reported time spent in each activity will be multiplied with its intensity to obtain average weekly energy expenditure (MET-h·wk.^− 1^) from each activity.

#### Follow-up

Infants’ weight, height, and head circumference will be obtained from examination records after 1, 4, 8, 12, and 24 months. The Ages and Stages Questionnaire (ASQ 3rd Edition) will be used to systematically screen the children for developmental and social-emotional delays in the crucial early years of life [51]. Five domains of development, including communication, gross motor, fine motor, problem-solving, and adaptive skills will be assessed through this questionnaire every four months (at 4, 8, 12, 16, 20, and 24 months postpartum). In conjunction with the questionnaire at 24 months, the Bayley Scale of infant and toddler development, 3rd edition (German version), will be used to assess motor (fine and gross) skills, language and cognitive development at this time point.

Furthermore, by using the Edinburgh Postnatal Depression Scale (EPDS Scale), postnatal depression will be recorded at weeks 6–8 after delivery [52]. In addition, questionnaires will be used to analyze maternal and paternal lifestyles after the intervention based on the German Health Interview and Examination Survey for Adults [53].

#### Statistics

The main variable (BMI at 24 months) will be analyzed by covariance analyses evaluated by the factor group, breastfeeding, and smoking as well as covariances of parental age, paternal BMI, socioeconomic status, breastfeeding, and potential pregnancy-induced diseases (e.g. gestational diabetes mellitus, pregnancy-induced hypertension (PIH)). The significance level alpha will be set at < 0.05 for all analyses. All confidence intervals will be estimated at 95%. Missing data will be calculated according to the LVCF approach (Last Value Carried Forward). Analyses will be carried out as per-protocol-analyzes and intention-to-treat analyses (ITT). Spearman and Pearson correlation procedure will be used to assess relationships between maternal data (physical activity in METs, eating habits, weight gain, blood samples) and neonatal data (birth weight, length, head circumference, Apgar scores, cord blood sample) as well as infants’ development. Multiple linear regressions will be performed for neonatal measures to determine correlations with maternal and paternal lifestyle factors. The model will include group (intervention yes/no) as well as maternal and paternal characteristics as possible confounders. Explained variance (r-squared) for the linear regression model will be reported as model fit statistic.

Statistical analysis will be performed using SPSS 24.0 data-analysis software (Statistical Product and Service Solutions 24.0) and data analysis will be blinded.

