## Methods/design

### Study design and setting

The ADEBAR study is a multi-centre, two-arm, randomized controlled trial (intervention versus control group) with the primary purpose of prevention. The program will take place at three hospitals in the Rhine region (Cologne, Düsseldorf, and Bonn) in Germany. The intervention period will last approximately 30–32 weeks (8 months) depending on the date of delivery. Mothers, fathers, and their offspring are being followed until the infant is two years of age. A schematic timeline and SPIRIT timetable of the study is presented in Fig. 1 and Fig. 2.

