**Fig. 2 Fig2:**
[figure not shown]
Schedule of enrolment, interventions, and assessments

We will perform a block randomization with a block size of six including an equal number of participants for all groups within each block (3:3). This ratio was chosen as it is expected to reduce bias and allocate participants evenly between the intervention and the control group [34].

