### Intervention

Depending on the place of recruitment, the nutrition counseling and exercise program will take place either in Cologne, Bonn or Düsseldorf in a conference room or at a gym, respectively. The intended group size will be 30 participants.

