#### Primary outcome

The primary outcome of this study will be the BMI of the infant at two years after birth assessed by German percentile [44].

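### The primary covariance model names its terms but omits centre in a three-centre trial, which costs some precision but causes no bias

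*Protocol article*

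**What the plan says.** Study design and setting: "The program will take place at three hospitals in the Rhine region (Cologne, Düsseldorf, and Bonn) in Germany". Recruitment is through obstetricians in the same three cities. Under Intervention: "Depending on the place of recruitment, the nutrition counseling and exercise program will take place either in Cologne, Bonn or Düsseldorf".

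The text under Fig. 2 describes permuted blocks of six, three women to each arm, expected to "allocate participants evenly between the intervention and the control group". It names no stratum and does not say whether the blocks run within centre.

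Under Statistics, the main variable "will be analyzed by covariance analyses evaluated by the factor group, breastfeeding, and smoking as well as covariances of parental age, paternal BMI", followed by "socioeconomic status, breastfeeding, and potential pregnancy-induced diseases". Centre is not among these terms, and no other section gives it a part in the analysis.

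**The concern.** Families in different cities may differ, and each city has its own delivery of the programme, so children's BMI could differ by centre. Centre is a baseline design factor: known for every woman at entry, never missing and untouched by treatment. The article does not defer its covariates. It fixes a list, and that list includes items that arise after randomisation, such as breastfeeding, while leaving this factor out.

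What is at stake is efficiency in a small comparison of 48 planned children. Any centre difference in BMI stays in the error term. Depending on how the blocks were run, it either adds real noise to the estimate or makes the reported standard error larger than the true one.

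**Working it through.** **Inputs from the article (Sample size, text under Fig. 2, Study design and setting).** 48 evaluable and 60 recruited women; 80% power; alpha 0.05; difference 1 kg/m²; effect size 1.0, hence SD = 1/1.0 = 1 kg/m²; blocks of six, 3:3; three centres.

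**Assumptions.** Two-sided test; three equal centres of 16; within-centre SD 1; centre means at -s, 0 and +s. The article gives no figure for s. The other covariates are ignored.

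**1. The plan's own figure.** Per arm, n = 2(1.960 + 0.842)²/1.0² = 15.7, so 16 per arm and 32 in total; the t-test needs 34. The stated 48 is not reproduced. With 24 per arm, power at d = 1.0 is 92.4%, and 80% power corresponds to d = 0.826. Both effects are used below. The point about centre does not depend on how 48 arose.

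**2. Closed form.** With centre in the model and balanced arms, SE = 2/√48 = 0.289. The variance between centres is 2s²/3, so omitting centre multiplies the model SE by k = √(1 + 2s²/3).
- s = 0.3: 2s²/3 = 0.06, which is 0.06/1.06 = 5.7% of total variance; k = 1.030.
- s = 0.5: 2s²/3 = 0.167, which is 0.167/1.167 = 14.3%; k = 1.080; unadjusted SE = 0.289 × 1.080 = 0.312.

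With one common block sequence, the estimate really does vary with SD of about 0.312, so type I error holds at 5%. At s = 0.5, power is that of a noncentral t with 0.826/0.312 = 2.65 and 46 df, or 74%. With blocks inside centres, the estimate varies with SD 0.289 while the model reports 0.312. The true type I error is then P(|t| > 2.013 × 1.080 = 2.174) = 3.5%.

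**3. Simulation of the same set-up (48 children, 20,000 runs per cell), which counts the 2 df and the imbalance.** Power is shown as centre omitted → centre included.

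| Centre means | Blocks | Power, d = 0.826 | Power, d = 1.0 | Type I error, omitted |
|---|---|---|---|---|
| no difference | common | 80.0 → 78.3% | 92.2 → 91.3% | 4.9% |
| no difference | per centre | 80.2 → 80.1% | 92.3 → 92.2% | 5.0% |
| ±0.3 SD | common | 77.8 → 78.6% | 90.8 → 91.5% | 5.1% |
| ±0.3 SD | per centre | 78.3 → 79.9% | 91.6 → 92.3% | 4.4% |
| ±0.5 SD | common | 73.4 → 78.1% | 88.0 → 91.1% | 5.2% |
| ±0.5 SD | per centre | 75.1 → 80.0% | 89.3 → 92.1% | 3.6% |

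**4. Check for bias (60 women, equal centres, centre assumed to carry 1%, 5% or 10% of variance).** With a common sequence and centre omitted, mean bias lies between -0.007 and 0.005 SD and type I error between 4.9% and 5.1%. The model SE of 0.257 matches the observed spread of 0.256 to 0.260. Chance centre imbalance moves a single trial's estimate with SD 0.025, 0.058 or 0.080, and the SE of 0.257 already covers that. With per-centre blocks, type I error is 5.1%, 4.2% and 3.0%.

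**The case against.** Much of the other side stands.

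- *The gain rests on assumed centre effects.* With the plan's implied SD of 1 kg/m², means at ±0.5 SD put the outer cities 1 kg/m² apart, the whole effect the trial hopes to find. Nothing in the article supports such a gap between hospitals in one region.
- *The baseline could be kinder.* If the SD of 1 is the total SD and already contains centre variance, power without centre stays at 80.0% for d = 0.826. Adjustment then gives 80.4%, 82.0% or 84.0% at centre shares of 1%, 5% or 10% (2 df ignored).
- *Other listed covariates*, such as socioeconomic status and paternal BMI, may absorb part of a centre difference.
- *Measurement.* The Follow-up section takes infant weight and height from examination records, but does not say that these differ by hospital.

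Three stronger readings are tempting. A reader might infer that centre confounds the arm contrast. Allocation is randomised, so it does not in expectation, and step 4 shows this. A reader might also infer that the randomisation was not stratified. The article is silent, and a condensed article may leave that to the full protocol. Finally, the attendance exclusions might fall unevenly by arm and centre in the per-protocol set. That is possible, but the article gives nothing from which to establish or size it.

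The objection does not remove the point itself: the article fixes a term list, and the list lacks a design factor.

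**Conclusion.** The point holds as a minor matter of precision and model specification. The direction of the effect is clear under either way of running the blocks: lost precision with a common sequence, a conservative test with blocks inside centres. Neither raises the false-positive rate.

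For 48 children and d = 0.83, including centre changes power by a loss of about 0 to 2 points if centres do not differ, a gain of about 0 to 2 points at ±0.3 SD, and a gain of about 4 to 5 points at ±0.5 SD. At d = 1.0 the last gain falls to about 3 points. All of this assumes equal centres, a within-centre SD of 1 and centre differences that the article does not report.

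**What to change.** In Statistics, add centre (Cologne, Düsseldorf, Bonn) to the primary covariance analysis as a fixed factor with 2 df. Fix before unblinding a rule for pooling a centre that contributes very few women.

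Leave the allocation procedure unchanged. The article describes no single list that could be re-run by centre. Altering allocation while recruitment continues, with participants aware of their arm and a published fixed block size, would also make the next assignment easier to predict at each site.

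The cost is one model term and, at worst, the loss of about 2 points of power given above. No extra women, visits or data are needed.

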Moreover, Reilly et al. [19] and Pato et al. [20] documented that paternal overweight is another risk factor for the development of juvenile obesity. In a cohort study among 4871 mothers, fathers, and their children, Gaillard et al. [21] evaluated the associations of paternal as well as maternal pre-pregnancy body mass index (BMI) with childhood body fat distribution and cardiometabolic outcomes. It was found that a higher maternal and paternal pre-pregnancy BMI was associated with an adverse cardiometabolic profile in offspring, although stronger associations were present for maternal pre-pregnancy BMI. These findings were confirmed by Santos Ferreira et al. [22]. In the last decade, research increasingly focused on epigenetic effects of lifestyle factors on offspring. In a systematic review, Dunford and Sangster [23] documented that newborns from obese fathers displayed altered methylation overall and significant hypomethylation at the Insulin-like Growth Factor 2 gene. Furthermore, altered offspring DNA methylation levels were associated with high maternal pre-pregnancy BMI [23]. Altered methylation outcomes at multiple imprint regulatory regions in children born to obese parents, compared with children born to non-obese parents, were also found by Soubry et al. [24]. They conclude that parental lifestyle factors and overnutrition have a preconceptional influence on the (re)programming of imprint marks during gametogenesis and early development [24].

Beside these findings, there is a lack of studies focusing on the effect of exercise or a combination of parental exercise and nutrition on the above-mentioned markers in newborns (venous cord blood) and especially on the long-term development of infants’ weight gain. Most previous studies have investigated maternal lifestyle changes but did not take paternal influences into account [25, 26]. Additionally, most of these interventions only used counseling sessions and information brochures [27, 28], and because of substantial methodological variations (e.g. content, duration, frequency, outcome parameters) results are inconsistent [29]. Paternal or transgenerational effects have predominantly been investigated in animal models with a main focus on nutrition [30–32]. In humans, only birth cohort studies have examined paternal lifestyle factors in combination with selected blood samples [33].

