### Participants

#### Inclusion and exclusion criteria

Women with a pre-pregnancy BMI [35] of ≥25 kg/m^2^, a singleton pregnancy, and a gestational age between 6 and 8 weeks, who were previously sedentary, are without pre-existing conditions such as heart disease, and who are currently not consuming alcohol or using medication for mental health disorders, will be recruited. At 13 weeks of pregnancy, women will receive a physician’s clearance to participate in physical activity. For further participation, they should have no contraindications to exercise during pregnancy according to the American College of Obstetrics and Gynecology [36]. Women with pre-existing diabetes, hypertension, or comorbidities known to affect fetal growth will be excluded from the study as well as women who are not proficient in German. Monthly obstetric check-ups will ensure maternal and fetal well-being.

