#### Nutrition counseling

Every nutrition counseling will be an extra appointment and is not part of the usual prenatal care appointments.

Pregnant women and their partners will be invited to a lecture about healthy diet during pregnancy at 8 weeks of gestation. This lecture will be followed-up by a 24 h dietary recall [38] to analyze individual energy intakes. This data will be entered and processed using the Prodi-Software® 6.2 (Science publishing society Stuttgart 2013, Germany) to calculate daily amounts of foods and nutrients. Based on this data, individual dietary counseling for the mother and, if possible, for the father will take place at 10 to 12 weeks of gestation. Individual counseling will be repeated at 16 and 24 weeks of gestation based on further 24 h dietary recalls. Additionally, group dietary counseling will consist of five sessions (weeks 14, 20, 30 and 36 of gestation, 8 weeks postpartum) and will be based on recommendations from the Network “Healthy Start – Young Family Network” [39]. Each session will last 60 min and will be led by a specially trained dietician.

After successful participation in the intervention, the families will receive a shopping voucher.

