### Outcome measures

#### Maternal measurements

Maternal anthropometric measurements of weight, height, BMI, skinfolds, and mid-arm and mid-thigh circumference will be assessed prior to the start of the program (week 8 of gestation), at weeks 14, 24, and 36 of gestation, at 8 weeks postpartum, and at 12 and 24 months postpartum.

Maternal body weight will be measured to the nearest kg using a digital scale (Tanita Corp., Tokyo, Japan) with the participant wearing casual clothing and no shoes. Maternal weight gain will be defined as the difference between self-reported pre-pregnancy weight and the last weight recorded before delivery. The IOM recommendations [45] will be used to classify excessive weight gain. Height will be measured to the nearest 0.1 cm using a metal stadiometer. Mid-arm and mid-thigh circumference will be measured to the nearest 0.1 cm with a non-extensible, flexible tape on the right side of the body. Skinfold thickness will be assessed by an observer using a Harpenden skinfold caliper (John Bull British Indicators Ltd., Harpenden UK) with a constant pressure of 10 g/mm^2^. The procedure will be carefully standardized and each measurement will be made in triplicate on the right side of the body. Four points will be measured to the nearest 0.2 mm at the triceps, thigh, subscapular and suprailiac site; the results will be averaged and incorporated into the eq. [46] to estimate percent body fat [47].

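### The primary ANCOVA adjusts for the father's BMI but omits maternal pre-pregnancy BMI, a baseline value available for every woman; the cost is precision and uncorrected chance imbalance, not bias

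*Protocol article*

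**What the plan says.** Primary outcome section: "The primary outcome of this study will be the BMI of the infant at two years after birth assessed by German percentile".

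Statistics section: this variable "will be analyzed by covariance analyses evaluated by the factor group, breastfeeding, and smoking", with "covariances of parental age, paternal BMI, socioeconomic status, breastfeeding" and pregnancy-induced diseases as the covariates. No form of maternal BMI is in either list. A later sentence in the same section admits characteristics of both parents as possible confounders, but it follows the multiple regressions for neonatal measures and does not extend to BMI at 24 months.

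Inclusion and exclusion criteria: "Women with a pre-pregnancy BMI [35] of ≥25 kg/m^2^, a singleton pregnancy". No upper limit is stated. Maternal measurements defines gestational weight gain as "the difference between self-reported pre-pregnancy weight and the last weight recorded before delivery", so the pre-pregnancy weight is self-reported.

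Background: in a cited cohort, higher BMI of either parent went with an adverse cardiometabolic profile in the offspring, "although stronger associations were present for maternal pre-pregnancy BMI". The same section links maternal overweight to obesity in childhood.

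Study design and setting: 1:1 randomization in blocks of six, with no mention of stratification by maternal BMI.

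**The concern.** The article does not leave the covariates to a later document. It lists them, and the list contains the BMI of one parent only. The omitted value is a true baseline variable, fixed before randomization, already needed to establish eligibility, and tied to offspring outcomes by the trial's own rationale. Since stratification by it is not mentioned either, neither the described allocation nor the described analysis deals with a chance difference between arms in how heavy the mothers were.

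In a large trial this would hardly matter. Here the plan counts on 48 evaluable women, about 24 per arm, so chance imbalances in baseline variables can be sizeable and any explained outcome variance is useful. A reader who finds the arms unbalanced on maternal BMI would also ask for an adjusted analysis. If that analysis is not prespecified, it becomes a choice made with the data in hand.

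**Working it through.** The omission itself is established by reading the sections side by side. The arithmetic only sizes it.

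**Inputs from the protocol article.** Sample size section: 48 women needed, 60 recruited, 25% drop-out, difference 1 kg/m², effect size 1.0, 80% power, significance level 0.05. The difference and effect size together imply an SD of 1 kg/m². Allocation is 1:1, so 48/2 = 24 per arm.

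**The plan's own figure.** Effect size 1.0, 80% power and two-sided 0.05 give 34 women in total by the t-test (32 by the normal approximation); one-sided, 28 (26). The stated 48 is not reproduced. At 24 per arm, power for an effect size of 1.0 is 92.4%. That discrepancy is a separate matter; 24 per arm is used below because it is the number the trial plans to evaluate.

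**Input not in the documents.** The correlation ρ between maternal pre-pregnancy BMI and child BMI at two years, given the other covariates. Range assumed: 0.2 to 0.4.

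**Chance imbalance.** The standard error of the between-arm difference in mean maternal BMI, in SD units, is √(2/n).
- n = 24: √(2/24) = 0.29 SD; 95% range ±1.96 × 0.289 = ±0.57 SD.
- Probability of more than 0.5 SD in either direction: 0.5/0.289 = 1.73, so about 8%.
- Probability of more than 0.25 SD: 0.25/0.289 = 0.87, so about 39%.
- With 25% of 60 lost, 60 × 0.75 = 45 remain, or 22.5 per arm: √(2/22.5) = 0.30 SD, much the same.

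**Effect of an imbalance on the estimate.** Shift in child BMI (SD units) ≈ ρ × imbalance.
- Imbalance of one standard error: 0.2 × 0.29 to 0.4 × 0.29 = 0.06 to 0.12 SD.
- Imbalance of 0.5 SD: 0.2 × 0.5 to 0.4 × 0.5 = 0.10 to 0.20 SD. With the implied SD of 1 kg/m², this is 0.10 to 0.20 kg/m², or 10% to 20% of the target difference.

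**Precision forgone.** Residual variance is multiplied by 1 − ρ².
- ρ = 0.2: 1 − 0.04 = 0.96, a cut of 4%, worth 1/0.96 − 1 = 4% more infants.
- ρ = 0.4: 1 − 0.16 = 0.84, a cut of 16%, worth 1/0.84 − 1 = 19% more infants.

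**Power at 24 per arm, two-sided 0.05** (effect size divided by √(1 − ρ²); residual degrees of freedom reduced from 46 to 45 when the covariate is added):

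| Effect size | No covariate | ρ = 0.2 | ρ = 0.3 | ρ = 0.4 |
|---|---|---|---|---|
| 1.0 (planned) | 92.4% | 93.3% | 94.4% | 95.9% |
| 0.82 | 79.4% | 81.0% | 83.0% | 85.8% |

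The second row is close to the effect that 48 women detect with 80% power.

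**The case against.** **The practical effect is small.** This largely stands. At the planned effect size, power is already above 92% and the covariate adds one to four percentage points. A one-standard-error imbalance moves the estimate by about a tenth of the target difference at most, and a large imbalance is uncommon. The upper end of the gain needs ρ = 0.4 among women who all have a BMI of 25 or more and whose pre-pregnancy weight is self-reported. Range restriction and measurement error may both lower the correlation.

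**The word may be a slip.** The list runs from *parental* age straight to *paternal* BMI, and the sentence names breastfeeding both as a factor and as a covariate, so it was not drafted tightly. *Parental BMI* may have been meant. The text cannot settle this. Either way, the model as printed excludes the mother's BMI and needs correcting.

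**Stronger readings that the documents do not support.**
- A reader might infer that the treatment effect would be biased. Allocation is randomized, so it is not, in expectation.
- A reader might infer that the Background calls maternal BMI the stronger predictor of this trial's outcome. The comparison there concerns cardiometabolic profile in one cited cohort, not BMI at age two and not only the children of overweight mothers.
- A reader might infer that infants will drop out of the analysis because fathers' BMI is missing, since the Nutrition counseling section says "individual dietary counseling for the mother and, if possible, for the father will take place". That qualifier applies to counseling. The Paternal measurements section schedules BMI at week 8 of gestation, 8 weeks postpartum and two years without it. Some missing values are plausible, because no criterion requires the father to take part, but no rate is given, and the handling of missing covariates may be left to the analysis plan, which is not shown.
- A reader might want the paternal covariates moved to a sensitivity model. The trial's stated interest in neglected paternal influence makes keeping them a legitimate choice.

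**Conclusion.** The point holds as an omission from the primary model. Paternal BMI is listed; maternal pre-pregnancy BMI, which eligibility makes available for every woman, is not. The consequence is limited to lost precision and uncorrected chance imbalance. The imbalance figures (standard error 0.29 SD, about an 8% chance of exceeding 0.5 SD) rest only on 24 per arm without stratification. The 4% to 16% cut in residual variance rests on an assumed correlation of 0.2 to 0.4, for which the documents give no value. This does not threaten the trial's validity. It is worth correcting because the adjustment is nearly free and is credible only if fixed before the outcome data are seen.

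**What to change.** In the Statistics section, add maternal pre-pregnancy BMI as a continuous covariate in the primary ANCOVA of BMI at 24 months. If *parental BMI* was intended, correct the word and name the mother's pre-pregnancy BMI and the father's BMI as separate terms. Leave the paternal covariates in the model.

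The cost is one degree of freedom and a change of wording. No new measurement is needed, because the value is already obtained to establish eligibility.

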## Background

The prevalence of overweight (Body Mass Index ≥25 kg/m^2^) and obesity (Body Mass Index ≥30 kg/m^2^) is increasing worldwide in every age group [1]. In Germany, the number of obese women of child-bearing age has increased especially over the last 25 years from 8.1% in 1990/1991 (25–34-year-old women) to 17.3% (30–44-year-old women) in 2014/2015 [2–4]. When obese women become pregnant they are at increased risk of several perinatal and postpartum complications such as excessive weight gain, gestational diabetes, preeclampsia, pregnancy-induced hypertension or fetal macrosomia [5, 6]. In addition, maternal overweight, excessive weight gain, and gestational diabetes during pregnancy are associated with obesity in childhood and adolescence in the child [7, 8]. Furthermore, children of overweight mothers are at increased risk for long-term metabolic dysfunctions such as hypertension, insulin resistance or metabolic syndrome [8, 9].

Epidemiological, clinical (animal), and experimental studies suggest that maternal lifestyle during pregnancy influences the metabolic, pro-inflammatory, and neurotropic pattern of the unborn child [10–12]. For instance, lifestyle factors have shown to affect adipokines, namely leptin, resistin and adiponectin as well as cytokines such as tumor necrosis factor alpha (TNF-α) and interleukin 6 (IL-6) [13, 14]. These, in turn, are involved in the regulation of maternal metabolic homeostasis and glucose metabolism, and the development of insulin resistance, metabolic syndrome, gestational diabetes mellitus, and hypertension [13].

Reports show that dietary patterns are associated with adiponectin, leptin, and insulin resistance [14–16]. For example, high intakes of fat are negatively associated with adiponectin levels and positively associated with leptin concentrations during pregnancy [16].

However, there are few reports about the interplay of lifestyle factors, in particular maternal exercise, during pregnancy and their effects on biomarkers in mother and offspring [17, 18].

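### The primary ANCOVA adjusts for the father's BMI but not the mother's, although the plan reports the maternal association as the stronger one; the cost is a modest loss of precision

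*Protocol article*

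**What the plan says.** Under Statistics, the protocol article specifies the primary analysis of child BMI at 24 months as "covariance analyses evaluated by the factor group, breastfeeding, and smoking", with "covariances of parental age, paternal BMI, socioeconomic status, breastfeeding, and potential pregnancy-induced diseases". Maternal BMI is in neither list. A later sentence in that section brings maternal and paternal characteristics in as possible confounders, but it describes the regressions for neonatal measures, not the primary outcome.

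The Background makes two statements about maternal weight. It says that "maternal overweight, excessive weight gain, and gestational diabetes during pregnancy are associated with obesity in childhood". It then describes a cohort in which both parents' pre-pregnancy BMI were related to childhood body fat distribution and cardiometabolic outcomes, "although stronger associations were present for maternal pre-pregnancy BMI".

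Maternal BMI is available. The inclusion criteria begin "Women with a pre-pregnancy BMI [35] of ≥25 kg/m^2^, a singleton pregnancy", with no upper limit stated. Maternal measurements lists "Maternal anthropometric measurements of weight, height, BMI, skinfolds" as taken before the programme starts. Randomisation is in blocks of six, and no stratification by BMI is described.

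**The concern.** A covariate earns its place in a randomised comparison by predicting the outcome. The plan's own rationale ranks the mother's BMI above the father's, and the covariate list does the reverse. The omitted variable is fixed before randomisation and is complete by design, because no woman can enter without it. The retained one depends on a father being available for measurement.

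The article states this list itself, so it is not a detail left to another document. At stake is some precision on the primary comparison in a trial planned for 60 women. There is also a practical risk: if the arms turn out to differ in maternal BMI, there will be pressure to add the term after the results are seen.

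**Working it through.** The plan states no figure for the value of any covariate, so there is none to reproduce. The check has two parts.

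**1. Is maternal BMI in the primary model under another name?** Taking the listed terms in turn: group, breastfeeding (listed twice), smoking, parental age, paternal BMI, socioeconomic status, pregnancy-induced diseases. None is maternal BMI. Gestational diabetes and pregnancy-induced hypertension may be related to it but do not replace it. No other section adds it.

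**2. What would adding it be worth?**

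Inputs from the article:
- 60 women recruited and 25% drop-out, so 60 × 0.75 = 45 children (23 and 22 per arm).
- About eight covariate terms besides group: breastfeeding 1, smoking 1, parental age 2 (mother and father), paternal BMI 1, socioeconomic status 1, pregnancy-induced diseases 2. The count depends on coding, so 7 to 10 is also shown.

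Assumption, not in the article: a *partial* correlation r of 0.2 to 0.35 between maternal BMI and child BMI at two years, given the other terms.

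With k other covariates, the expected variance of the group effect after adding one more, divided by the variance before, is

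(1 − r²) × (N − 3 − k) / (N − 4 − k).

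For N = 45 and k = 8 the second factor is 34/33 = 1.0303.

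| Partial r | 1 − r² | Variance ratio | Change |
|---|---|---|---|
| 0.15 | 0.9775 | 1.007 | 0.7% worse |
| 0.20 | 0.9600 | 0.989 | 1.1% better |
| 0.30 | 0.9100 | 0.938 | 6.2% better |
| 0.35 | 0.8775 | 0.904 | 9.6% better |

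Break-even is where r² = 1/(N − 3 − k) = 1/34, so r = 0.17. With k = 7 it is √(1/35) = 0.169; with k = 10 it is √(1/32) = 0.177.

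Expressed as children: 45 × (1/0.989 − 1) = 0.5 at r = 0.2, and 45 × (1/0.904 − 1) = 4.8 at r = 0.35.

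The result depends little on N. With the 48 women the article says are needed (k = 8), the factor is 37/36, the ratios are 0.987 and 0.902, and break-even is √(1/37) = 0.164. With all 60, the factor is 49/48, the ratios are 0.980 and 0.896, and break-even is √(1/49) = 0.143.

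**The same loss seen as chance imbalance.** The arm difference in maternal BMI, in SD units, has a standard deviation of √(1/23 + 1/22) = 0.298. In a comparison without other covariates, a one-SD imbalance moves the estimate by r × 0.298 SD of child BMI: 0.060 at r = 0.2 and 0.104 at r = 0.35. The standard error of the unadjusted difference is 0.298 SD, so the shift is r standard errors. It is already part of the variance that adjustment would remove and must not be counted a second time.

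**The case against.** The strongest objection is that the gain may be nil. The correlation that matters is partial: paternal BMI, socioeconomic status and the pregnancy-induced diseases plausibly share information with maternal BMI. Entry at 25 kg/m² or more narrows its range, which tends to lower the correlation. A partial r below 0.17 is possible, and there the extra term costs slightly more than it returns, in a model already crowded for 45 to 60 children. This stands. It limits the size of the claim but does not explain why the father's BMI was chosen over the mother's.

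The Background statement is also weaker than it may look. It reports one cohort, on body fat distribution and cardiometabolic outcomes, and compares only the two parents. A reader might infer that the plan calls maternal BMI the strongest predictor of BMI at age two; it does not.

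Third, *paternal BMI* follows directly on *parental age* and may be a slip for parental BMI. The article cannot settle this. As written the mother is left out, and a one-sentence correction is needed in either case.

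Finally, a reader might infer that the primary estimate is biased, or that imbalance is a second harm on top of lost precision. Neither follows. Omitting a baseline variable leaves the randomised intention-to-treat comparison unbiased on average, and the variation due to imbalance is already in the confidence interval. The per-protocol analysis is different. The drop-out criteria remove women for complications, preterm birth, low attendance or missed blood tests, and the Background says obese women are at higher risk of complications. Maternal BMI could then differ between the retained groups for reasons other than chance.

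**Conclusion.** The point holds as an inconsistent and easily corrected covariate choice. The primary model, as listed, adjusts for the parental BMI with the weaker reported association and omits the one with the stronger, which is known for every woman at entry. For the intention-to-treat analysis the consequence is a modest loss of precision: about 1% to 10% of the variance, or roughly 0.5 to 5 children out of 45. This rests on an assumed partial r of 0.2 to 0.35 and eight other covariate terms; below r of about 0.17 there is no gain. The documents give no correlation, so the size cannot be fixed more closely. For the per-protocol analysis the omission matters somewhat more, because randomisation no longer protects that comparison. The change is worth making because it is nearly free and follows the plan's own reasoning, not because the primary result would otherwise be invalid.

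**What to change.** In the Statistics section, name maternal pre-pregnancy BMI as a continuous covariate of the primary ANCOVA, beside paternal BMI. If the intended term was parental BMI, replace *paternal BMI* with maternal and paternal BMI as two separate covariates. Fix the wording before the analysis is unblinded, so that the choice cannot depend on how the arms turn out.

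The cost is one sentence and one degree of freedom. No new data are needed, since the variable is collected at screening. Adjustment does not restore the protection of randomisation to the per-protocol comparison; it removes only the part of any difference that runs through maternal BMI.
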